## Participants

Based on sample size calculations, a reduction in the proportion of wards with high bed alarm use requires 15 wards to achieve 80% power with a two-tailed alpha of 0.05. The nesting of wards within health services (3 wards per service on average) requires adjustment for this design effect. A pilot study we conducted in Victoria (Brusco et al., 2021) identified an intra-class correlation of bed alarm use of 0.10, indicating that we will require 18 wards nested within 6 health services. We will recruit these 18 wards across 6 public or private metropolitan health services in Australia. The control arm will be recruited from different health services, and will also consist of 18 wards to match the intervention arm. The same inclusion and exclusion criteria will be applied to both the intervention arm and control arm.

Inclusion criteria: wards with a mobilisation alarm use rate of at least 3% will be eligible for participation in the study. This will be determined by daily audits over a 2-week period.

Exclusion criteria: paediatric, emergency, intensive care, and mental health wards, as well as residential aged care facilities within health services will not be recruited for this study.

In the intervention arm, 2 groups of individual participants will be recruited:

1. Up to 5 staff members from each participating ward and the falls prevention portfolio manager will be recruited to provide feedback on their attitudes and perceptions of falls prevention, mobilisation alarms, and this project. This will be conducted at 4 times points during the project.
2. A random selection of patients who are 36 hours prior to discharge in each ward will be recruited to complete 2 brief questionnaires to provide feedback on their hospital stay. This will be conducted on a weekly basis.

In the control arm, 1 group of individual participants will be recruited:

1. Up to 5 staff members from each participating ward and the falls prevention portfolio manager will be recruited to provide feedback on their attitudes and perceptions of falls prevention, mobilisation alarms, and this project. This will be conducted at 3 times points during the project.

### Hospital Wards

Following approvals, we will ask site representatives to nominate wards that match the inclusion and exclusion criteria. For each nominated ward, a 2-week audit will be conducted to determine eventual eligibility: daily audits of mobilisation alarm use rate will be tallied to confirm the minimum 3% use rate. We anticipate approximately 1-2 months to screen the wards and recruit staff on the wards to participate in the qualitative component of the project.

### Hospital Staff

Wards that are deemed eligible for the study will be informed of the project by the site liaison at each health service during a weekly staff meeting following site special approvals are granted. The site liaison will be named principal investigator for each site, they will be named as the primary contact person for the study at their health services and their contact details (phone number and email) will be available on the participant information and consent forms (PICF). Staff, including the falls prevention portfolio manager at the health service, will be given a copy of the participant information and consent form (PICF) outlining their expected involvement. The site liaison will follow up at the next weekly meeting and obtain signed consent forms from up to 5 ward staff who are interested. Staff may also contact the site liaison via the provided phone number or email to express their interest to participate in the study. A copy of the PICF with contacts details for queries and complaints will be provided at the end of participation.

### Pre-discharge Patients

Recruitment of patients who are 36 hours pre-discharge will be conducted in the intervention arm by the onsite research assistant on a weekly basis during the study period. A ward will be randomly chosen each week, hospital records will be used to identify patients in participating wards who will be discharged in the next 36 hours. Research assistants will approach these patients, explain the project, and ask for consent to participate. Patients will be given 5 minutes to consider their participation. Participants will be asked to sign a PICF before any data is collected. A copy of the PICF with contacts details for queries and complaints will be provided at the end of participation. This process will begin as soon as the study begins and continue until all wards have undergone mobilisation alarm reduction/removal and the trial ends.

## Procedures

### Intervention Arm – Eliminating and/or Reducing Mobilisation Alarms

To assess the effectiveness of mobilisation alarms, their use will be eliminated or reduced in tertiary hospital wards. The elimination and reduction of alarms will be the intervention. A stepped-wedge design will be used for intervention. Pairs of wards (clusters) will be randomised into either eliminated (0%) or reduced (<3%) mobilisation alarm use, they will then enter the intervention conditions in sequential order month by month, until all wards are under the intervention conditions (Figure 1). Baseline assessments will be conducted over a 1-month before the first cluster begins intervention, the entire intervention period will last 9 months, with different clusters under intervention for different lengths of time. One week prior to each cluster beginning intervention, the ward staff will be interviewed for their perception of the study. Follow-up assessments will be conducted at 1 month and 13 months after the end of intervention. Participating health services and wards will be required to comply with the intervention condition they are assigned to, weekly auditing of mobilisation alarm use rate will be conducted to ensure they are eliminated and/or reduced as required. During the period of intervention, falls rates and other related outcomes will be collected on a weekly basis by the site research assistant (Table 1). The rate of newly diagnosed COVID cases will also be documented each week, as this continues to be an ongoing concern in hospitals and may interfere with daily procedures that affect falls management in wards.

[figure not shown]

**Figure 1. Stepped-wedge design proposed in the current study.**

### Control Arm – Observing Mobilisation Alarms and Provision of Evidence

The control arm will follow the same schedule as the intervention arm, but with no disinvestment interventions. Data will only be collected at 3 time points: baseline, 1-month follow up, and 12-month follow up (Figure 2).

[figure not shown]

**Figure 2. Data collection schedule for the control arm.**

### Staff Workshop and Interviews

Around 5 staff from each participating ward and the falls prevention manager at each health service will be interviewed at 4 time-points:

1. Baseline (intervention and control arms) – a workshop describing the most up-to-date research evidence for mobilisation alarms will be given in the form of PowerPoint presentation and infographic video. Following this, staff will be asked about their attitudes towards mobilisation alarms and participation in the study.
2. 1 week before intervention condition begins (intervention arm only) – staff will be asked again about their attitude towards participation in the study.
3. 1 month following the end of intervention (intervention and control arms) – staff will be informed of the findings of the study, and will be asked about their experience in participating in the study and if and how their attitudes towards mobilisation alarms have changed.
4. 12 months following the end of intervention (intervention and control arms) – staff will be asked about their attitude towards mobilisation alarms and if there have been any practice changes for their use.
5. Practice implementation questionnaire (intervention and control) – the falls prevention portfolio will be asked to complete a brief rating scale (~5 minutes) about the implementation of evidence-based falls prevention practice at their health service at each data collection point described above.

The workshop and interviews will have the option of being conducted over online platforms to avoid in-person researcher visits to health services. The synchronous option will use the zoom.us platform for the presentation and to conduct group interviews with the participating staff. The interview will be voice-recorded for later analysis. The asynchronous option will involve uploading the presentation to an online video-hosting platform, which will allow participating staff access in their own time, and feedback from staff will be sought via online questionnaires/surveys.

### Pre-discharge Patients

A random sample of patients across participating wards in the intervention arm will be requested to complete two surveys at 36 hours prior to their discharge, this will be conducted throughout the duration of the study. One survey will be the question “Overall, how would you rate the care you received while in hospital?”, response categories for this item are Very Good, Good, Average, Poor, Very Poor. The second survey will be the 10-question Pittsburgh Sleep Quality Index (Carpenter & Andrykowski, 1998).

### Health Service Implementation Strategies

The health services are anticipated to carry out support strategies for the implementation of alarm use change in this study. For the purpose of understanding intervention fidelity, members of the research team who will be visiting study sites and contributing to the coordination of study activities will take field notes at strategy meetings.

### Falls Prevention Guideline Documents

The official health service falls prevention and falls alarm use documents may or may not change following the trial and provision of evidence from the trial. Therefore, official guidelines and documents will be accessed from each health service for the periods before the trial (prior to April 2023), immediately after the trial (anticipated February 2024), and at the 12-month post-trial follow-up (anticipated February 2025). These documents are accessible via the staff intranet, site investigators will be responsible for accessing them.

## Outcome Measures and Data Collection

| **Table 1. Outcome measures and their data collection approach in the intervention arm.** | | |
| --- | --- | --- |
| **Outcome** | **Outcome Type** | **Data Collection Approach(es)** |
| Rate of Falls | Primary Clinical Outcome | Extraction from hospital records  Interview with nurse unit managers (NUM) |
| Rate of roll-outs from low-low beds | Secondary Clinical Outcome | Extraction from hospital records  Interview with nurse unit managers (NUM) |
| Rate of falls-related injuries | Secondary Clinical Outcome | Extraction from hospital records |
| Patient satisfaction with care –  Victorian Patient Satisfaction Survey (Draper, Cohen, & Buchan, 2001) | Secondary Clinical Outcome | Interview with patient sub-sample |
| Patient sleep quality –  Pittsburgh Sleep Quality Index(Carpenter & Andrykowski, 1998) | Secondary Clinical Outcome | Interview with patient sub-sample |
| Rate of health service code greys | Secondary Outcome - Non-falls Related Adverse Events | Extraction from hospital records |
| Rate of newly developed pressure injuries (since admission to ward) | Secondary Outcome - Non-falls Related Adverse Events | Extraction from hospital records |
| Rate of medication error | Secondary Outcome - Non-falls Related Adverse Events | Extraction from hospital records |
| Rate of hospital readmission within 30 days | Secondary Outcome - Non-falls Related Adverse Events | Extraction from hospital records |
| Proportion of patients with mobilisation alarms | Secondary Outcome – Intervention Fidelity | Direct observations of ward beds |
| Rate of use of “other” confounding falls-prevention interventions | Secondary Outcome – Intervention Contamination | Direct observations of ward beds |
| Casemix payments to hospital | Secondary Intervention Outcomes | Extraction from hospital records |
| Procedures subsequent to falls-related injury | Secondary Intervention Outcomes | Extraction from hospital records |
| Staff attitudes to involvement in trial | Other Secondary Outcomes | Interview with NUMs and ward staff at the start of the trial |
| Staff concerns regarding transition from Current condition to either Reduced or Eliminated conditions | Other Secondary Outcomes | Interview with NUMs and ward staff prior to transition |
| Staff experiences of transition and intervention | Other Secondary Outcomes | Interviews with NUMs and ward staff at 1-month and 12-months post-trial follow-ups |
| Knowledge translation and implementation of evidence-based practices (Stages of healthcare implementation rating scale, unpublished) | Other Secondary Outcomes | Falls prevention portfolio manager completion of rating scale |

# Data Management

## Data Coding

Data will take the form of hard copies of surveys and written notes made during interviews, and soft copies of electronic records of falls and mobilisation alarm-related data on tablet computers. Individuals that provide data will be assigned a code on documents to protect their privacy, for example P123 for patients who complete surveys before discharge, CL123 for staff who participate in interviews. Identifying information such as name and diagnosis will not be included in the data.

## Data Access

Any access to the data following storage will need to be informed either the project manager or chief investigator, with documentation of each personnel who requested data, the data they requested access to, and reason for access.

## Data Use

The data collected for this project is for the sole purpose of research. Analysis and interpretation of the data will be for the primary purpose of addressing the research objectives raised in this proposal. If data is requested for the purpose of other research objectives, the chief investigator will consider each request on its individual merit.

## Data Archive

The data for this project will be archived accordingly to the above described steps following the conclusion of the project.

## Data Analysis

A reduction in the proportion of wards with high bed alarm use from 100% to 50% requires 15 wards per group to achieve 80% power with a two-tailed alpha of 0.05. The nesting of wards within health services (3 wards per service on average) requires adjustment for this design effect. Our disinvestment pilot study (Brusco et al., 2021) identified an intra-class correlation (ICC) of bed alarm use of 0.10, indicating we require 18 wards per group nested within the 6 health services. With this sample size, the intervention will have 86% power to detect a 10% relative difference in fall rates with a mean baseline of 8 falls (standard deviation=4) per month per ward, and an ICC of fall rates between wards of 0.63 based upon 1000 bootstrap power analysis simulations (Stata MP version 14.0).

Participating wards will be matched by type (acute, subacute) into clusters. Wards in each cluster will undergo the same period of intervention, allowing for comparison of varying degrees of disinvestment. Falls and alarm use rate across time will allow for the examination of the feasibility of disinvesting mobilisation alarms and its effects on falls rate and whether these effects can be sustained.

The content of post-workshop interviews and recordings of interviews with health service staff will be thematically analysed. The software NVivo will be used to aid in the coding, linking, categorising, and theme identification. Interview transcripts will be analysed independently by at least two researchers.

The cost-benefit analysis is calculated by summing the costs of the benefits and then subtracting the costs of implementation. The primary cost-benefit analysis will include the direct and indirect benefits, the secondary cost-benefit analysis will only include the direct benefits. Data will be analysed and presented as a total across the six participating health services as well as individually for each health service. Reporting for each health service individually will provide data on the range of implementation costs borne by the different health services. Average cost per health service will be reported as a mean value with a standard deviation, and the costs for the different health services will be compared with an independent t-test, where p<0.05 will be used to determine statistical significance.

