## Methodological Approach

This will be a concurrent, nested, randomised stepped-wedge study with a mixed methods and non-inferiority design (Figure 1). Half of the wards (n=18) will be assigned to the intervention arm, the other half to the control arm. All wards in the intervention arm will begin under the same “usual care” condition, pairs of wards will begin the disinvestment condition at different time points, which will allow for comparisons of the ward with itself under different conditions: a) usual care of utilising the mobilisation alarms, and b) removing or reducing its use. Randomisation will determine whether each ward undergoes a removed or reduced mobilisation alarm condition, and the timing at which they phase into this condition. All wards in the control arm will be observed during the same time period, with no disinvestment process in place, but will receive the evidence arising from the intervention arm.

The mixed methods design combines quantitative and qualitative methodologies for the data collected and their analysis. Quantitative methods will be used to collect data for the rate of use of mobilisation alarms and other falls prevention strategies, resources allocated to the implementation of these strategies, and the clinical outcomes for participating wards. A narrative inquiry approach will be used to collect data regarding stakeholder acceptability of the disinvestment process; stakeholders will include health professionals and patients.

This study will also be a non-inferiority trial, this means we will try to prove that the removal/reduction of mobilisation alarms will not result in worse clinical outcomes. Therefore, a non-inferiority margin will be agreed upon with all health services in the intervention arm. The margin will be a specific rate of falls (averaged across all health services) that is just below the usual average rate of falls that is deemed unacceptable. For example, if the average number of falls that occur across Victoria is Y per week, then 150% more than Y falls per week while alarms are reduced/removed will see a stop to the entire project.

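### The 86% power claimed for a 10% relative difference in falls is not delivered by the stepped wedge the protocol describes; with month effects it is roughly 12–25%, depending on what SD 4 means

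*Protocol*

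**What the plan says.** The protocol's Data Analysis section sizes the trial on alarm use. The comparison "requires 15 wards per group to achieve 80% power with a two-tailed alpha of 0.05", and an ICC of 0.10 raises this, "indicating we require 18 wards per group nested within the 6 health services". It then makes a claim for falls at that sample size: "the intervention will have 86% power to detect a 10% relative difference in fall rates with a mean baseline of 8 falls". The count in a ward-month is given an SD of 4, and the correlation and method behind the claim are stated as "an ICC of fall rates between wards of 0.63 based upon 1000 bootstrap power analysis simulations". The model, number of periods and sidedness of that simulation are not given.

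The design is fixed in other sections. Methodological Approach puts 18 wards in the intervention arm, crossing over in pairs. The Intervention Arm section says "they will then enter the intervention conditions in sequential order month by month, until all wards are under the intervention conditions", after a one-month baseline and over nine months in all. The 18 control wards come from other health services and never cross over; for them, "Data will only be collected at 3 time points: baseline, 1-month follow up, and 12-month follow up". Table 1 makes the rate of falls the primary clinical outcome.

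**The concern.** A 10% change on a baseline of 8 is 0.8 falls per ward-month, a small effect against an SD of 4 with only 18 wards crossing over. In a stepped wedge the treatment effect is partly confounded with calendar time, so adjusting for month costs further precision. An 86% chance of detecting so small a change looked too high for the inputs printed beside it.

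The sentence tells the ethics committee and the health services how fine a change in the primary clinical outcome the trial can resolve. If it is wrong by this much, a true 10% rise in falls would more often than not go undetected by the comparison the sentence describes.

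**Working it through.** **Inputs (protocol).** I = 18 wards, 9 sequences of 2; T = 1 + 9 = 10 months; 180 ward-months, 90 of them exposed. Effect δ = 0.10 × 8 = 0.8. SD 4, so variance 16; ICC 0.63. Two-sided 5% is borrowed from the alarm-use calculation, since none is stated for falls.

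**The plan's own figures.** The alarm-use sample size reproduces: 15 per group for 100% v 50% with a continuity correction, then 15 × (1 + 2 × 0.10) = 18. The falls power of 86% does not.

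**Stepped wedge with month effects.** Hussey–Hughes variance, with within-ward variance s² and between-ward variance t²:

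var = I·s²(s² + T·t²) / [(IU − W)s² + (U² + ITU − TW − IV)t²]

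Here U = 90, W = 4 × (0² + … + 9²) = 1140 and V = 2 × (1² + … + 9²) = 570. So IU − W = 1620 − 1140 = 480, and the second bracket is 8100 + 16200 − 11400 − 10260 = 2640.

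If SD 4 is the total SD, t² = 16 × 0.63 = 10.08 and s² = 16 × 0.37 = 5.92:

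var = 18 × 5.92 × 106.72 / (480 × 5.92 + 2640 × 10.08) = 11372 / 29453 = 0.386; SE = 0.621

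Power = Φ(0.8/0.621 − 1.96) = Φ(−0.67) = 25%.

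The same formula under each reading (detectable difference = 2.80 × SE / 8):

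| Reading | s² | t² | SE | Power for 10% | Detectable at 80% |
|---|---|---|---|---|---|
| SD 4 total | 5.92 | 10.08 | 0.621 | 25% | 22% |
| Poisson within, total variance 16 | 8 | 8 | 0.713 | 20% | 25% |
| SD 4 between wards | 9.40 | 16 | 0.783 | 17% | 27% |
| SD 4 within wards | 16 | 27.2 | 1.022 | 12% | 36% |

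A Poisson simulation with ward and month effects agreed: about 21% for a rate ratio of 0.9 and 13–19% for 1.1.

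**More generous readings.**
- No month effects: 1/var = (U − φV)/s² − U²/[IT(s² + T·t²)], with φ = t²/(s² + T·t²). For SD 4 total this is 36.16/5.92 − 8100/19210 = 5.69, so SE 0.419. Power is Φ(1.91 − 1.96) = 48% two-sided and Φ(1.91 − 1.645) = 60% one-sided 5%. Across the four readings, two-sided power is 21–48%.
- Control wards added at their stated time points, with month effects (SD 4 total): 34–38%.
- The two follow-ups counted as eleventh and twelfth exposed periods, control data included, no month effects, one-sided 5%, SD 4 total: 71%. This stacks every favourable choice.

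**A check without a mixed model.** Ninety ward-months at 8 falls give 720 unexposed falls, and 648 exposed at a rate ratio of 0.9. With no ward variation and no trend, SE(log RR) = √(1/720 + 1/648) = 0.0541 and |log 0.9| = 0.1054, so z = 1.95 and power is about 49%.

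**What 86% would need.** With SD 4 total and month effects: an ICC near 0.94, or an SD near 1.7 at ICC 0.63. Without month effects: an ICC near 0.86, or an SD near 2.5. The simulation error of 1000 runs is √(0.86 × 0.14/1000) = 1.1 percentage points, so chance does not explain the gap.

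**The case against.** The best defence is that the simulation is not shown. The protocol states neither its model, periods nor sidedness, and an analysis plan may hold them. In a trial described as non-inferiority, a one-sided test would be usual. If all 36 wards stepped, with no month effects and a one-sided 5% test, power would be 85.4%, within simulation error of 86%. Likewise, 23 months of monthly data on 18 wards, without month effects and one-sided, gives 84.4%. Both contradict the protocol: control wards never cross over, and monthly periods end after the ninth step. The defence therefore suggests how 86% might have arisen, but does not make it true of this trial. What does stand is that no single replacement figure can be called the trial's power, because it depends on assumptions the protocol leaves open.

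A reader might also infer that SD 4 and ICC 0.63 contradict each other, because a within-ward variance of 5.92 lies below the Poisson variance of 8, capping the ICC at 0.50. That holds only if SD 4 is the total SD and falls are not under-dispersed. If SD 4 is the between-ward SD, the within-ward variance is 9.40 and there is no conflict. The fault shown is an undefined SD; the total-SD reading is simply the one most favourable to the trial.

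Finally, a reader might infer that a non-significant difference would be taken as proof of safety. The protocol plans a non-inferiority margin, so that is not its stated criterion.

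**Conclusion.** The statement of 86% power is wrong for the design in which it stands and should be corrected before anyone relies on it. Under a two-sided 5% month-effects analysis of the 18 wards over ten months, power for a 10% relative difference is about 25%, 20%, 17% or 12%, according to how SD 4 and the within-ward variance are read. Dropping the month effects, which is not safe under a secular trend, gives at most 48% two-sided or about 60% one-sided; even the stacked reading reaches only 71%. The size of the shortfall depends on model, sidedness and the meaning of SD, but its existence does not.

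The conclusion is confined to the claim about a 10% difference. It does not show that the trial cannot exclude a large increase: with month effects, power to exclude an extra 4 falls per ward-month (50% of 8) is 97% or more under all four readings when the true difference is zero.

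**What to change.** Rerun the simulation for the design in Methodological Approach and the Intervention Arm section: 18 wards, nine pairs, one baseline month and nine monthly steps, with month effects and a within-ward variance no smaller than the mean. State beside the result the analysis model, the number of periods, the sidedness and alpha for falls, whether SD 4 is total, between-ward or within-ward, and the scale on which ICC 0.63 is defined. Then replace the 86% with the result.

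Under a two-sided 5% test, with within-ward and between-ward variances of 8 and 8, or of 9.40 and 16, the new sentence would report about 17–20% power for a 10% relative difference, or a difference of about 25–27% detectable with 80% power. If SD 4 proves to be the within-ward SD, the figures are about 12% and 36%.

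The work is one simulation rerun and one rewritten sentence. The real cost is that the stated power becomes much less favourable, and the sponsor must then either accept the larger detectable difference openly or justify another basis for the falls conclusion.
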